## Appropriateness of the statistical methodology

The appropriateness of the statistical model for each of the variables outlines in the sections, 'Primary Endpoint and Analysis' and 'Secondary Endpoint and Analysis' be assessed prior to conducting analyses. This would include, but is not limited to, checking for outliers, checking the histogram for normal distribution, checking the homogeneity of variance and checking expected cell frequencies. If necessary, transformation of severely skewed variables and/or use of nonparametric alternative analyses will be performed.

### **9.4 Missing Data**

Missing data will be replaced using the last observation carried forward (LOCF) method. The last observed value will be used to impute all the missing values for that person. In the event of substantial missing data (>10% of the expected data set), multiple imputation will be used as an additional method for handling missing values. The purpose of carrying out multiple imputation would be to provide a sensitivity analysis to the LOCF method. If there is a significant difference between these methods, the multiple imputation approach is considered to be more reliable for large amounts of missing data. A previous study supported the use of modern imputation techniques as opposed to simpler techniques such as the LOCF method or case deletion method. Multiple imputation has also been recommended for use in RA trials for a variety of outcome measures including measures of disease activity.

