### **9.3.2 Primary Endpoint and Analysis**

Cetrorelix has a rapid onset and offset effect; therefore we have chosen an early primary endpoint. The primary endpoint is the change in disease activity score (DAS28CRP) on Day 5b (12 hours after the last injection [time point when LH and FSH levels are expected to be lowest]).

The primary variable will be analysed by ANCOVA, linear regression with last measurement (in this case day 5b) as the dependent variable and treatment and baseline measurement as independent variables (covariates).

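### LOCF is the primary missing-data method despite a drug effect the protocol expects to come and go quickly, and an undefined comparison made after both results are seen decides whether multiple imputation is preferred

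*Protocol*

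**What the plan says.** - **Default method (9.4):** "Missing data will be replaced using the last observation carried forward (LOCF) method". It applies without limit: "The last observed value will be used to impute all the missing values for that person".
- **Contingency (9.4):** "In the event of substantial missing data (>10% of the expected data set), multiple imputation will be used as an additional method". Its role is stated: "The purpose of carrying out multiple imputation would be to provide a sensitivity analysis to the LOCF method".
- **Which result to trust (9.4):** "If there is a significant difference between these methods, the multiple imputation approach is considered to be more reliable for large amounts of missing data".
- **The protocol's own evidence (9.4):** "A previous study supported the use of modern imputation techniques as opposed to simpler techniques such as the LOCF method or case deletion method". The next sentence adds that multiple imputation has been recommended for RA trials, including for disease activity measures.
- **Time course (9.3.2):** "Cetrorelix has a rapid onset and offset effect; therefore we have chosen an early primary endpoint".
- **Primary analysis (9.3.2):** "The primary variable will be analysed by ANCOVA, linear regression with last measurement (in this case day 5b) as the dependent variable", with treatment and baseline as covariates.
- **Schedule (Figure 1 and 6.7):** after screening, CRP/ESR is taken on Days 1, 2, 5b, 10 and 15, and at no visit between Day 2 and Day 5b.
- **Withdrawal (8.4):** a patient who asks to withdraw has the final-visit examinations before any new therapy is added. In Figure 1 the final visit includes joint counts, VAS and CRP/ESR.

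**The concern.** The LOCF assumption of a constant value contradicts the reason given for the choice of endpoint. If the effect builds over five days of dosing and then fades, a value from Day 2 or baseline understates the Day 5b effect, and a Day 5b value overstates the effect at Days 10 and 15. The ITT population (9.2.2) includes everyone who received any injection, so filled values enter the primary ANCOVA. They are then treated as if observed, with no allowance for the uncertainty of imputation.

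The second problem is that section 9.4 does not settle which method governs. Multiple imputation is introduced as a sensitivity analysis and then described as more reliable if the two methods differ significantly. No criterion for that difference is given, and it can be judged only once both results are known. The base of the 10% trigger (patients, visits or variables) is not given either.

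At stake are the size of the Day 5b estimate, the reading of the Day 10 and Day 15 secondary results, and a clear prior statement of which primary result counts.

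**Working it through.** **1. The protocol's own figure.** Inputs from 9.1: difference 0.6, SD of change 1.0, two-sided alpha 0.05, power 0.80. N = 2(1.96 + 0.842)² × 1² / 0.6² = 43.6, so 44 per group, as stated. The allowance takes 44 to 49, and 5/49 = 10.2%. The loss the trial plans for therefore lies next to the 10% trigger.

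**2. What is carried to Day 5b.** DAS28CRP needs a CRP value. With none scheduled between Day 2 and Day 5b, the last complete score before Day 5b is from Day 2 (after one dose) or baseline, unless an exit examination was done under 8.4.

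**3. Dilution at Day 5b.** Let d be the proportion missing in each arm and f the share of the 0.6 effect present in carried values. Both are assumed, because the protocol gives neither. Expected difference = 0.6 × [1 − d(1 − f)].

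| d | f = 0 | f = 0.5 |
|---|---|---|
| 5% | 0.570 | 0.585 |
| 10% | 0.540 | 0.570 |
| 20% | 0.480 | 0.540 |

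**4. Power under the planned analysis.** With an SD of change of 1.0 and equal variances at the two visits, each visit has variance 1/[2(1 − ρ)], and the ANCOVA residual variance is (1 + ρ)/2. That is 0.75 at ρ = 0.5 and 0.90 at ρ = 0.8, against 1.0 for an unadjusted comparison of changes. The protocol gives no ρ, so a range is shown. Simulation used 49 per arm, a true effect of 0.6, carried patients given their baseline value (f = 0), and 20,000 runs per cell.

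| ρ | None carried | 5 of 49 per arm | 10 of 49 per arm |
|---|---|---|---|
| 0.50 | 92% | 88% | 82% |
| 0.65 | 90% | 85% | 79% |
| 0.75 | 88% | 84% | 78% |
| 0.80 | 87% | 82% | 77% |

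The mean estimate was about 0.54 with 5 carried and 0.48 with 10 carried, in line with step 3.

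**5. Unequal loss with no drug effect.** If both arms improve by m between the carried visit and Day 5b, the LOCF bias is m × (loss on cetrorelix − loss on placebo). For assumed m of 0.3 to 0.6 and losses of 15% against 5%, this is 0.03 to 0.06 units against the arm with the greater loss. The direction depends on who leaves.

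**6. Day 15, as an alternative scenario.** Suppose the effect has gone by Day 15 and 10% of the active arm carry a Day 5b value containing the full 0.6. LOCF then shows 0.10 × 0.6 = 0.06 of benefit that is no longer there. With SD 1.0 and 49 per arm the standard error is √(2/49) = 0.20, so this is about 0.3 of a standard error. If half the effect remains, the bias is 0.03.

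**7. Type I error.** A simulation of 3,000 null trials, with values missing completely at random and Day 2 carried forward, gave the following.

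| Missing | LOCF | Multiple imputation | Methods disagree on significance |
|---|---|---|---|
| 11% | 5.3% | 5.0% | 2.2% |
| 20% | 5.4% | 5.6% | 3.3% |
| 30% | 4.6% | 4.8% | 3.5% |

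Under these conditions neither method alone departs visibly from 5%, but the two can point different ways.

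**The case against.** **Exit examinations.** A patient who withdraws at their own request on Days 3 to 5 can have a complete DAS28CRP at exit, and LOCF would carry that value. This stands and reduces the problem. It does not remove it: the sentence in 8.4 does not expressly cover withdrawals decided by the investigator or patients who simply do not return.

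**Power.** A reader might infer that LOCF takes the trial below its stated 80% at the planned drop-out. An unadjusted comparison of 0.54 with SD 1.0 and 49 per arm does give about 76%. The planned analysis adjusts for baseline, however, and step 4 shows 82–88% in the same worst case. Power dips below 80% only at about 20% carried with the higher correlations.

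**Double counting.** The Day 5b dilution and the false Day 15 benefit cannot both be charged to the same 10% of patients. They are alternatives. The protocol also does not say that the effect on DAS28 has gone by Day 15: 9.3.2 ties the timing to LH and FSH, and 4.1 says repeated doses prolong the antagonism.

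**Free choice of p-value.** A reader might infer that the sponsor may report whichever method is significant. Unrestricted choice would give a type I error of about 6.3%, 7.1% and 6.4% at 11%, 20% and 30% missing. The text does not grant that choice. It points only towards multiple imputation, and if multiple imputation always prevailed on disagreement, alpha would not be inflated. What remains is an undefined rule applied after the results are seen.

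**The protocol's view of multiple imputation.** It is called more reliable only for large amounts of missing data and where the methods differ. It is never said outright to replace the LOCF result, and that silence is part of the ambiguity.

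**Conclusion.** The point holds. The primary missing-data method rests on an assumption that the protocol's own account of the drug contradicts, and the evidence cited in the same section favours the alternative. The size is modest at the planned loss: 0.60 falls to 0.54 at Day 5b with 10% missing and no effect in carried values, or to 0.57 if carried values hold half the effect. In the alternative scenario, a false 0.06 appears at Day 15. These figures rest on assumed missingness and an assumed time course, and the bias has no fixed direction when loss differs between arms. A shortfall against 80% power at the planned drop-out is not shown. Separately, the rule for which method governs is undefined, depends on the results, and has a trigger close to the planned drop-out rate. The protocol itself fixes these choices, so they are not details left to a later analysis plan.

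**What to change.** Pre-specify one primary approach that applies whatever the amount missing:

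- multiple imputation, done by arm and using baseline and the DAS28 components from all visits, followed by the planned ANCOVA; or
- a likelihood-based repeated-measures model of DAS28CRP, with the treatment contrast read at Day 5b.

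Keep LOCF only as a labelled sensitivity analysis. Delete the sentence that turns on a significant difference between methods, and delete the 10% trigger. Make the change before unblinding.

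The cost is revised wording in 9.4 (and in 9.3.2 if the repeated-measures model is chosen) and a little more programming. No visit, assessment or patient is added, and the sample size stays as it is.

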## **9.5 Safety Data Analyses**

All AEs will be coded and tabulated by body system and the preferred term for individual events within each body system and will be presented in descending frequency. AEs will also be tabulated by severity and relationship to cetrorelix. SAEs will be summarised separately.

Associated laboratory tests such as haematology, liver function tests, kidney function tests will be grouped and presented together. For each laboratory test, all individual patient values will be listed and values outside the standard reference range will be highlighted. Marked abnormalities will be tabulated for each laboratory test by treatment group.

The change from baseline for each of the vital sign variables for each individual patient will be listed and summarised using descriptive statistics.

## **9.6 Interim Analysis**

No interim analyses have been planned.

## **9.7 Replacement Policy**

No patient who discontinues the study for whatever reason will be replaced.

## **9.8 Criteria for termination of the trial**

The trial will be terminated if there are unacceptable side effects of the intervention such as a serious drug related AE or if there is a significant worsening of the RA disease (increase in DAS28 of more than 3.2 points) by day 3 in a large proportion of patients.

The investigator (sponsor) reserves the right to terminate the study at any time. In terminating the study, adequate consideration will be given to the protection of the patients' interests.

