## 5.2 Inclusion Criteria

A subject will be eligible for study participation if he/she meets the following criteria:

- Age  $\geq 18$  years
- Fulfilment of the revised 1987 American College of Rheumatology (ACR) criteria for the classification of RA.
- Moderate or severely active RA, defined as a DAS28  $\geq 3.2$  and at least two of the following criteria:  $\geq 6$  painful joints,  $\geq 3$  swollen joints, ESR  $\geq 20$ mm/h, and a C-reactive protein  $\geq 10$ mg/L
- Prednisolone  $\leq 7.5$ mg/day permitted if stable for at least 4 weeks prior to baseline, NSAIDs permitted if stable for at least 2 weeks prior to baseline; disease modifying anti-rheumatic drugs (DMARDs) permitted if stable for at least 8 weeks prior to baseline
- A negative pregnancy test for women of childbearing potential prior to start of treatment
- Use of reliable method of contraception e.g. intra-uterine devices or sheaths by all sexually active patients. If the patient is abstinent, they must agree to stay abstinent or use reliable contraception if sexual activity commences.
- Menstruating women may enter the study in the early follicular phase of their menstrual cycle only
- Able and willing to give written informed consent and to comply with the requirements of the study protocol

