#### **6.4.1 DAS28 Assessment**

In order to evaluate the eligibility of the patients the treating physician will calculate a DAS28 score at screening. A total of 28 joints will be assessed: shoulders, elbows, wrists, 1st-5th MCP, 1st IP and 2nd-5th PIP joints and knees. Joint tenderness and swollenness is classified as present or absent. The number of tender and/or swollen joints is reported.

DAS28-ESR/CRP can be therefore calculated based on the following formula:

$$\text{DAS28} = 0.56 * \text{sqrt}(\text{tender28}) + 0.28 * \text{sqrt}(\text{swollen28}) + 0.014 * \text{VAS global} + 0.70 * \ln(\text{ESR}) \text{ or } [0.36 * \ln(\text{CRP}+1) + 0.96]$$

where sqrt denotes the square root, ESR denotes erythrocyte sedimentation rate in mm/h, CRP denotes C-reactive protein in mg/L, and TJC and SJC are tender joint count and swollen joint count defined as above. Global disease activity measured on a visual analogue scale of 100mm will also be obtained.

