## **6.7 Study Assessments**

Complete efficacy and safety assessments will be made on Days 1 (baseline), 2, 5b, 10, and 15.

The sequence of assessments will be as follows:

1. Patient reported assessments: patient's global assessment of disease activity (VAS), pain (VAS), HAQ
2. Other efficacy assessments: joint counts, physicians global assessment of disease activity
3. Safety assessments
4. Laboratory samples for safety and efficacy will be obtained as in Figure 1

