## **8 SAFETY ISSUES**

### **8.1 Adverse Events**

*Adverse events (AEs) include the following:*

- All suspected adverse drug reactions.
- All reactions from medication overdose, withdrawal, sensitivity or toxicity.
- Apparently unrelated illnesses, including the worsening of a pre-existing illness
- Injury or accidents.
- Abnormalities in physiological testing or physical examination findings that require clinical intervention or further investigation.
- Laboratory abnormalities that require clinical intervention or further investigation unless they are associated with an already reported clinical event.

*Pre-existing conditions:*

In this trial, a pre-existing condition will not be reported as an AE unless the condition worsens.

*Study Disease:*

Deterioration in the study disease and signs and symptoms thereof will not be reported as AEs unless the patient discontinues the study due to the sign or symptom or patients meet the specified criteria for stopping the trial (section 9.8).

*Adverse Event Reporting Period:*

The adverse event-reporting period for this trial begins on inclusion in the trial and ends at the final clinical visit.

*Adverse Event Reporting:*

Each patient will be questioned about AEs at each clinic visit following initiation of treatment. The investigator is to report all directly observed AEs and all AEs spontaneously reported by the patient. The AE will be noted as either treatment related or other. AEs will be stratified by sex, to map sex specific differences. AEs spontaneously reported by the patient or observed by the investigator during the trial will be recorded in the CRF.

AEs will be graded according to the Common Terminology Criteria for Adverse Events (CTCAE), version 3. Details of these criteria can be accessed at <http://ctep.cancer.gov>.

AEs not listed by the CTCAE will be graded using the following criteria.

Grade 1 (Mild): Discomfort noticed but no disruption of normal daily activity

Grade 2 (Moderate): Discomfort sufficient to reduce or affect normal daily activity

Grade 3 (Severe): Inability to work or perform normal daily activity

Grade 4 (Life-threatening or disabling): Represents an immediate threat to life. Such events should also be reported as serious events.

Relationship of the AE to the treatment should be assessed and noted as follows:

Relationship on AE Form:

- Yes (related)
- No (unrelated)

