## **8.4 Discontinuation Criteria**

A patient should be withdrawn from trial treatment at any time if, in the opinion of the investigator, it is medically necessary, or if it is the wish of the patient. Patients may

withdraw at their own request at any time during the trial period. Should a patient make such a request, the reason should be recorded in the CRF and final visit examinations be performed before addition of new therapy. If a medicine, which is not allowed in the trial, is needed, patients must be withdrawn from the trial. If concomitant therapy needs to be changed in the opinion of the consultant rheumatologist, the patient will be withdrawn from the trial. The consultant rheumatologist, in consultation with the patient, will decide the future course of treatment.

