## **9 STATISTICS**

### **9.1 Sample Size**

Assuming a difference of 0.6 unit reduction from baseline in mean DAS28 score on cetorelix compared with placebo and an underlying standard deviation for the changes from baseline of 1.0 unit (from previous data), we calculated that

$$N = 2(Z_{\alpha} + Z_{\beta})^2 \sigma^2 / \delta^2,$$

where  $\delta = \mu_2 - \mu_1 = 0.6$

$$N = 2 (1.96 + 0.842)^2 1^2 / 0.6^2$$

**N= 44** per treatment group

To allow for drop-outs, **49 patients in each group** were considered adequate. The significance is 0.05 (two-tailed) with a power of 0.8.

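### The RA-worsening limit in 9.8 (a DAS28 rise of more than 3.2) is set too high to serve its purpose, and 8.1 ties a single patient's adverse-event reporting to it

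*Protocol*

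**What the plan says.** Section 9.8 gives two grounds for termination besides the sponsor's right to stop at any time. One is unacceptable side effects, such as a serious drug-related event. The other is significant worsening of RA by day 3 in a large share of patients, with the individual worsening defined as an "increase in DAS28 of more than 3.2 points". The share is not given as a number, and the limit has no stated derivation.

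Section 8.1 (Study Disease) refers to the same rule. Deterioration of RA and its symptoms "will not be reported as AEs unless the patient discontinues the study due to the sign or symptom", or unless "patients meet the specified criteria for stopping the trial (section 9.8"). These are the only two exceptions.

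Three other places set the scale:
- Section 9.1 plans on a difference of 0.6 and "an underlying standard deviation for the changes from baseline of 1.0 unit (from previous data").
- The EULAR table in 9.3.1 cuts DAS28 change at 0.6 and 1.2.
- Everywhere else, 3.2 is a DAS28 level: the entry floor in 5.1 and 5.2, the EULAR table row in 9.3.1, and low disease activity in 9.3.3.

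On timing, section 6.7 states: "Complete efficacy and safety assessments will be made on Days 1 (baseline), 2, 5b, 10, and 15". The schedule in Figure 1 has joint counts and VAS on day 3 but no CRP or ESR.

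**The concern.** A stopping limit is useful only if it can be reached under the harm it is meant to detect. A rise of 3.2 is more than five times the effect the trial is sized for (3.2/0.6 = 5.3). If it is out of reach under a clear adverse effect on RA, the only quantified worsening criterion in the protocol gives no warning.

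The cross-reference in 8.1 carries the problem into adverse-event recording. It asks whether one patient meets a criterion defined on a share of all patients, at a rise very few could show. A patient who flares but stays in the study then has no adverse event recorded for it. Safety in RA is the first-listed secondary aim (3.2), and 4.1 says this kind of suppression has not been studied in RA before.

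**Working it through.** **Inputs.** Limit 3.2 (9.8); SD of change 1.0 and planning effect 0.6 (9.1); largest change category 1.2 (9.3.1); 49 patients per arm (9.1); DAS28 formula (6.4.1). Assumed: change is normally distributed, and the SD of 1.0 applies by day 3 (range 0.8 to 1.5 shown).

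**The plan's own figure.** 9.8 offers no calculation to reproduce. The sample size that uses the same SD does reproduce: 2 × (1.96 + 0.842)² × 1² / 0.6² = 43.6, so 44 per group.

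**Relative size.** 3.2/1.0 = 3.2 SD; 3.2/1.2 = 2.7 times the largest change category.

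**Share of patients above the limit.** P(rise > 3.2) = 1 − Φ((3.2 − m)/SD), where m is the mean worsening.

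| m | SD 0.8 | SD 1.0 | SD 1.5 | Expected of 49 (SD 1.0) |
|---|---|---|---|---|
| 0 | 0.003% | 0.07% | 1.6% | 0.03 |
| 0.6 | 0.06% | 0.5% | 4.2% | 0.2 |
| 1.2 | 0.6% | 2.3% | 9.1% | 1.1 |
| 2.0 | 6.7% | 11.5% | 21.2% | 5.6 |

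**Chance that the rule is met.** This depends on what the large share means. The calculation counts the cetrorelix arm only (49 patients), the reading most favourable to the rule, and uses the binomial tail with the shares above.

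| Assumed share | m = 1.2, SD 1.0 | m = 2.0, SD 1.0 | m = 1.2, SD 1.5 |
|---|---|---|---|
| 10% (5 of 49) | 0.5% | 68% | 47% |
| 20% (10 of 49) | under 0.001% | 5.0% | 1.2% |

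For 20% of the arm to be expected above the limit at SD 1.0, mean worsening must be 3.2 − 0.84 = 2.4 units.

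**Ceiling of the scale (no distribution needed).** With 28 tender and 28 swollen joints and VAS 100, the joint and VAS terms reach (0.56 + 0.28) × √28 + 0.014 × 100 = 5.845.
- DAS28CRP with CRP 100 mg/L (assumed): 5.845 + 0.36 × ln(101) + 0.96 = 8.47. A rise of more than 3.2 is impossible from a baseline above 8.47 − 3.2 = 5.27.
- DAS28ESR with ESR 100 mm/h (assumed): 5.845 + 0.70 × ln(100) = 9.07. It is impossible from a baseline above 5.87.

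The documents do not say how many patients start above these values.

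**Chance variation at lower limits (no drug effect, SD 1.0).**
- More than 1.2: 1 − Φ(1.2) = 11.5% of patients, about 11 of 98 at one visit. Over the four complete post-baseline visits, between 11 (fully correlated) and 38 (independent).
- More than 1.8: 1 − Φ(1.8) = 3.6%, about 3.5 of 98 at one visit and at most about 13 over four.

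**The case against.** The strongest reply is that patients are not left unprotected, and this stands. The side-effect ground and the right to stop at any time remain in 9.8. The discontinuation route in 8.1 is the one that works in practice, because 8.4 says: "If concomitant therapy needs to be changed in the opinion of the consultant rheumatologist, the patient will be withdrawn from the trial". A flare that forces a change of therapy thus ends in withdrawal and becomes reportable. What goes unrecorded as an adverse event is a flare managed without withdrawal, and its DAS28 is still collected as outcome data.

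A reader might infer from the table that the rule can never act. The documents do not support that. They do not fix the share or the arm in which it is counted, and a 10% reading in the cetrorelix arm makes the rule likely to be met at a mean worsening of 2.0, or close to even at 1.2 with SD 1.5.

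A reader might also infer that a rise of 3.2 is out of reach for patients in general. That is too strong as well. 9.8 does not say which DAS28 is meant, and the ceiling is higher for the ESR version. The entry floor of 3.2 admits patients with ample room to rise, and the two-of-four rule in 5.2 can be met through ESR and CRP with few joints involved.

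The missing fraction and look schedule are not counted as errors, since they may stand in a statistical analysis plan or the monitoring plan. The objection to the number 3.2 is unaffected, because the protocol itself states it.

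**Conclusion.** The point holds for the stated rise and for the cross-reference. At SD 1.0 a mean worsening of 1.2, twice the planning effect in the wrong direction, puts about 1 of 49 cetrorelix patients above the limit, so the worsening rule practically never acts there. It could act only under very large harm, a larger SD, or a low reading of the share counted in the cetrorelix arm. Patients with high baseline activity cannot reach it: above about 5.3 for DAS28CRP or 5.9 for DAS28ESR, at the assumed laboratory values. The second exception in 8.1 is nearly empty and applies a trial-level criterion to one patient.

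This rests on normality, on the planning SD holding at day 3, and on assumed readings of the share. That 3.2 is a DAS28 level carried over as a change is a plausible origin, but the protocol does not say so.

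Severity is minor to moderate: one safeguard is weak while others remain, and the primary analysis and sample size are unaffected.

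**What to change.** **Section 9.8.** Replace 3.2 with a clinically chosen, reachable rise, for example more than 1.2, the protocol's own largest change category. Score it on the complete day 2 DAS28, because CRP and ESR are not drawn on day 3. Count it blinded over all patients, so that 9.6 (no interim analysis) can stand. Let a crossing trigger a safety review instead of automatic termination. Choose the rise and the fraction together: with no drug effect 11.5% of patients exceed 1.2 at SD 1.0 (6.7% to 21.2% for SD 0.8 to 1.5), so the fraction must sit well above that. An elaborate sequential scheme is not needed.

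**Section 8.1.** Replace the reference to 9.8 with a patient-level criterion, for example a DAS28 rise of more than 1.8. List these events separately from the adverse-event count compared between arms in 9.3.3 item 11, so that chance variation in DAS28 does not enter that test.

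**Cost.** One amendment with ethics committee and medicines agency approval (11.1), a periodic blinded count, and some chance flags: about 3.5 of 98 patients per visit at more than 1.8 with SD 1.0. Counting over both arms dilutes a signal confined to cetrorelix; that is the price of staying blinded.
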